## Abstract

**Background:**

Massive rotator cuff tears are challenging injuries, and there is currently a clinical need to improve treatment outcomes and reduce the re-tear rate. In recent years, both mechanical augmentation with acellular matrices, such as acellular dermal matrix and orthobiologics, including concentrated humeral bone marrow or subacromial bursal tissue, have been proposed to enhance clinical outcomes of the rotator cuff repair.

**Methods:**

Seventy-two patients (aged 18–65 years) with repairable large to massive rotator cuff tears involving supraspinatus and infraspinatus tendons are randomized in a 1:1 ratio to receive either acellular dermal matrix alone (Group A: mechanical augmentation) or a combination of acellular dermal matrix enriched with bone marrow concentrated from the humeral head and subacromial bursal tissue (Group B: mechanical and biological augmentation). The primary outcome is the re-tear rate at 1 year follow-up, assessed via MRI using Sugaya classification. Secondary outcomes include clinical and functional evaluations using the Constant-Murley, Visual Analogue Scale, PASS and DASH scores at 1, 3, 6, and 12 months. Work loss and restricted activity days and adverse events are also recorded. Biological and biomechanical characterization of acellular dermal matrix, concentrated humeral bone marrow and subacromial bursa are measured and correlated with clinical outcomes to find parameters affecting the tendon repair.

**Expected outcomes:**

A more robust tendon-to-bone reattachment, vascularization and cell colonization are expected to face to patient’s functional demand and to diminish the psychological and economic burden resulting from re-tears, revisions, additional rehabilitation and missed work. The use of decellularized human matrix provides benefits, since it derives from donation of human tissue, with low production and distribution costs in comparison with commercially available acellular matrices.

**Clinical trial registration:**

[clinicaltrials.gov], identifier [NCT05855759].

## Background

1

Rotator Cuff (RC) tears are among the most frequent soft-tissue injuries affecting the shoulder, and can lead to pain, disability and premature osteoarthritis. RC repair is characterized by a highly variable re-tear rate, ranging from 24% up to 94% depending on age, chronicity, tear size, and repair technique, among other factors (1). The treatment of massive RC tears is particularly challenging because of poor tendon quality, hypo-vascularization and the formation of a repair scar tissue that is not biomechanically competent (1, 2). During recent years, the clinical interest in biological acellular matrices is increasing because of their capacity in providing the ideal biologic and structural milieu for tissue integration and regeneration. Matrices of animal and human origins have been investigated in preclinical researches and low evidence clinical studies with variable results and the lack of conclusive proof of efficacy (1). To date, none of the available augmentation techniques have achieved the regeneration of a tendon-bone attachment that is structurally and functionally non-inferior to the native enthesis. An improvement in surgical repair and cost-effectiveness is reported in a randomized controlled trial with a collagen based bioinductive implant compared to repair alone (3). Augmentation with cross-linked acellular porcine dermal patch is reported to provide a non-inferior failure load and reduced inflammatory response compared to porcine small intestine submucosa patch in an ovine model study at 2 years follow-up (4).

Instead, augmentation of large-to-massive RC tears with human dermal allografts is associated with superior functional and structural outcome when compared with conventional primary repair (5).

In this scenario, an acellular dermal matrix (ADM) from human donors is developed (PCT n. IB/2008/002753): ADM is obtained from multi-organ and/or multi-tissue donors, the decellularization process removes the cellular components responsible for rejection in the recipient, while preserving its structural, biomechanical, and biological integrity, which confer bioactivity, biomechanical competence, and regenerative capacity. The patented ADM scaffold is used for many applications in medicine and surgery (tendon, ankle reconstruction, breast and gynecologic surgery, dermatology, dentistry, urology and ophthalmology), with good results concerning safety and clinical outcomes (6–10). ADM is extensively characterized and tested in various steps of preclinical *in vitro* and *in vivo* experimentations (11–13) and in a previous work transplanted into seven patients affected by massive **R**C lesions: at 1 year of follow up, all patients showed an improvement in symptoms and no side effects, inflammatory or septic complications occurred (2). From these preliminary results, the rationale for this trial is to gain evidence-based and robust data regarding ADM implantation in a larger cohort of patients, thanks to excellent mechanical and biological properties. Moreover, a growing interest is focusing on ADM, aiming to combine the biological potential to be integrated into the patient’s repaired tendon and mechanical strength, to preserve the repaired tendon from early failure.

The use of orthobiologics is gaining interest due to the biological eutrophic effects and the homeostatic influence of several products, ranging from blood-derivatives as platelet-rich-plasma to minimally manipulated mesenchymal stromal cells (MSCs) or connective tissue progenitors (14).

Hernigou et al. (15) reports structural healing improvements evaluated with ultrasound and MRI at 6 months and significant lower re-tears at 10 years when RC repairs are augmented with bone marrow aspirate concentrate. More recently, a Randomized Controlled Trial is performed to compare outcomes after arthroscopic RC repair with and without bone marrow aspirate augmentation. At one year, the control group shows significantly greater evidence of rotator cuff re-tear on MRI according to Sugaya classification (57% vs. 18%; *P* < 0.001), but failure rates and functional outcomes are comparable at final follow-up (16).

Proximal humerus is reported as a suitable source of MSCs, with samples of bone marrow aspirate from the proximal humerus yielding a significantly higher amount of Colony Forming Units (CFUs) when compared with samples of bone marrow obtained from the ilium (17, 18). From our preliminary studies about 10−250 × 10^6^ adherent mesenchymal stromal cells/ml of humeral bone marrow have been isolated, that are ranges in line with literature and the manufacturer’s product specifications (19).^1^

Subacromial bursa (SAB) is also identified as a source of connective tissue progenitors and vasculature supporting factors, and SAB-derived cells showed mesenchymal potential and higher proliferation compared with cells derived from concentrated bone marrow (20, 21). Moreover, the use of SAB is reported for biological augmentation of RC healing with good results, both as an intact tissue, or as a processed tissue in combination with other injective products (22–24). From culturing the subacromial bursal tissues we obtained about 20–80 CFU/well by seeding 2 × 10^3^ cells even in line with scientific literature available (20, 21).

A clinical trial on ADM arthroscopic augmentation for RC massive tear repair has never been performed as well as, to the best of our knowledge, on the combination of acellular human matrices with orthobiologic products derived from the patient’s shoulder anatomic district, which could improve outcomes reducing the re-tear rate.

## Hypothesis and aims

2

The hypothesis of our study is that the combination of mechanical and biological augmentation could potentially lead to a superior quality of the repair, with improved functional and structural results and lower re-tears and failure rate. The secondary hypothesis is that there will be relationships among the specific biological characteristics of ADM, SAB and concentrated humeral bone marrow (cHBM) from patients and the post-operative clinical outcomes.

The main aim is to evaluate the therapeutic efficacy in terms of re-tear rate at 12 months from arthroscopic implantation of ADM in association with orthobiological stimuli for the augmentation of massive RC repair in comparison with the ADM alone. The secondary aim is the *in vitro* biological characterization of SAB and cHBM, as surgical discharge materials from each patient, and biomechanical competence of ADM to determine specific correlations with the obtained clinical outcome investigations.

## Methods

3

### Study setting

3.1

A double-blinded randomized controlled trial (RCT) is designed to compare the efficacy of ADM in association with orthobiological stimuli, the one-step concentrated humeral bone marrow and vascularized subacromial bursa versus ADM alone for the augmentation of massive RC tears arthroscopic repair. This study is a single-center, double-blind RCT conducted in a highly specialized center for orthopedic surgery, the IRCCS Rizzoli Orthopedic Institute (Bologna, Italy), and performed by the close collaboration between the Unit dedicated exclusively to Shoulder and Elbow Surgery and the Unit of Surgical Sciences and Technologies devoted to preclinical biological and biomechanical investigations. The Regional Skin Bank (AUSL Romagna, Cesena, Italy) produces ADM in Good Manufacturing Practice certified environments for transplant use. The trial is approved by the Ethical Committee of Area Vasta Emilia Centro (CE AVEC) (protocol number 0004860) and registered at clinicaltrials.gov (NCT05855759).

After signing a study specific informed consent, each participant is assigned randomly with ratio 1: 1 to RC repair with ADM implantation (Group A), or ADM implantation with orthobiologics, consisting of autologous cHBM and SAB (Group B).

### Eligibility criteria

3.2

Patients are recruited according to the following criteria.

Inclusion criteria:

Male or female patients, aged between 18 and 65 years.Large to Massive Rotator Cuff tear involving supraspinatus and infraspinatus tendons with tendon retraction ≤ Thomazeau 3 and fatty infiltration ≤ Goutallier 3 at pre-op MRI.Possibility to obtain tendons reduction at footprint and complete repair.Patients’ ability and consent to participate in clinical and radiological follow-up.Signature of informed consent.

Exclusion criteria:

Shoulder Osteoarthitis, even mild according to Samilson.Adhesive capsulitis.Symptomatic acromioclavicular arthritis.Previous RC repair in the affected shoulder.Current or past hematological disorders.Chronic steroid assumption or comorbidities affecting healing.Patients with malignancy, rheumatic diseases. uncompensated endocrine diseases.Patients abusing alcoholic beverages or drugs.Pregnancy and lactation.Inability to cope with post-op rehabilitation regimen.

### Allocation and randomization

3.3

A total of 72 eligible patients are allocated to receive either a combination of mechanical (ADM) and biological (cHBM + SAB) augmentation after RC repair or mechanical augmentation with ADM alone, in a 1:1 ratio (36 patients for each group of treatment) based on a computer-generated randomization.

The randomization list is created using an online randomization list generator^2^ with a permuted block of variable length from 2 to 6. Enrolled patients are randomly assigned to the massive RC repair augmented with autologous cHBM, SAB and ADM arm (group B) or to the ADM augmentation alone (group A), as comparator arm, following a pre-determined randomization list. Patients and outcome assessors are blinded, while the surgeon knows the group assignation of the patient the day of surgery, opening a dedicated closed envelope.

### ADM procurement

3.4

Acellular dermal matrix harvesting, processing, and distribution are performed according to national rules on tissues for transplantation. Briefly, samples of human dermis are harvested from multi-organ and multi-tissue donors, processed for decellularization (PCT n. IB/2008/002753) and stored in liquid nitrogen at −180 °C. The day before surgery, ADM is defrosted and conserved at a temperature of 4 °C until its use.

### Intervention

3.5

All patients are treated by a single orthopedic surgeon with established experience in sports medicine shoulder surgery and orthobiologic procedures. The procedure is performed in a single step in the operating room with patients in beach-chair position under general anesthesia. The affected shoulder is sterilely prepared and draped as for standard arthroscopic RC repair.

In all patients a standard shoulder arthroscopy is performed, and all patients undergo a comprehensive arthroscopic evaluation to confirm the RC tear characteristics and assess repairability.

#### Group A

3.5.1

After a standard diagnostic arthroscopy, RC repair is carried out. Posterosuperior RC repair is performed using non-metallic anchors and, when necessary, subscapularis repair is also performed. If biceps pathology is identified during diagnostic arthroscopy, arthroscopic biceps tenotomy or tenodesis is concurrently performed. Once the arthroscopic repair is completed, the ADM is inserted into the subacromial space via an accessory lateral portal and sutured with non-metallic anchors and suture tape and on top of the repaired RC. Standard closure of the portals is then performed and an abduction sling is positioned.

#### Group B

3.5.2

For Group B patients, before starting the arthroscopic procedure, a stab incision is performed, a diamond tip trocar is inserted into the proximal humeral epiphysis and humeral bone marrow is harvested using two 30 ml syringes coated with heparin for a total of 60 ml. The bone marrow harvesting time requires approximately 10 min, and while on the surgical field the rotator cuff repair begins, the bone marrow isconcentrated by an automatic close system (Harvest BMAC, Terumo BCT Inc., with a dedicated harvesting and concentrating disposable kit costing approximately 1500 Euros). After the 15-min working cycle a total of 10 ml of bone marrow autologous concentrated (cHBM) is available.

In Group B, at the beginning of the shoulder arthroscopy, approximately 4 mg of SAB are harvested, processed with chopping technique and stored in sterile saline solution for subsequent implant. The cuff is then repaired and the graft positioned, as previously described for group A. After the completion of the mechanical augmentation and suture of the arthroscopic portals, in group B patients, 8 ml cHBM and about 3 ml of the processed SAB are injected into the repair site. For each group B patient, 2 ml cHBM and 1 ml SAB samples, as residual materials from the operating room, are sent to the laboratory for the count of mesenchymal stromal cells, clonogenic ability by colony forming unit-fibroblast test, phenotypical characterization by flow-cytometry and trilineage differentiation. From each group, ADM samples are tested for mechanical and biological competences: maximum load, tensile strength, Young’s modulus, stiffness, growth factors release and extracellular matrix protein contents are measured.

### Post-operative protocol

3.6

Patients are normally discharged on postoperative day 1, based on patient condition and pain control is prescribed as needed. All patients undergo the same rehabilitative protocol, consisting in 1-month of sling abduction with no shoulder movements. The second month post-operative patients gradually dismiss the sling, and start passive movements with physiotherapist for 2 weeks, followed by active exercises avoiding reinforce for the next 6 weeks. Exercises for muscular strengthening are allowed 3 months after surgery, along with full recovery of daily and working activities.

### Outcomes

3.7

#### Primary outcome

3.7.1

The primary outcome is the re-tear rate on MRI at 1 year follow up, with the rational of verifying the integrity of the repaired tendon after several months of daily and working regular life, and detecting scaffold integration at the implant site. The integrity of the repair in post-operative MRI will be assessed with Sugaya classification.

#### Secondary clinical outcomes

3.7.2

Secondary outcomes include clinical and functional assessments, performed pre-operatively and at 1-, 3-, 6- and 12-months post-op using the Constant-Murley, Visual Analogue Scale (VAS), PASS and DASH scores. Secondary outcomes also include work loss and restricted activity days and adverse events.

#### Secondary research outcomes

3.7.3

The *in vitro* biological characterization of orthobiologics from each patient, cHBM and SAB, are evaluated in term of cellular yield, proliferation ability, mesenchymal potential, surface marker expression and multilineage differentiation; SAB is also characterized by histological and gene expression approaches to define its characteristics for angiogenetic, inflammatory and regenerative factors. Finally, ADM is evaluated for its contribution in terms of growth factors release, extracellular matrix contents, and biomechanical properties (maximum load, tensile strength, Young’s modulus and stiffness). The biological characterizations of cHBM and SAB and the biomechanical characterization of ADM are used in correlation with the clinical ourcomes, in order to identify any parameter that might have influenced the clinics.

### Participant timeline

3.8

A screening of potential candidates is performed by the members of the Shoulder and Elbow Unit among patients affected by a massive RC tear. If eligibility is possible, patients are informed of the study protocol and they are offered to enter in the study, with adequate time to decide. If they accept to enter the clinical trial, they sign informed consent and complete the baseline clinical scores. Follow-up assessments are performed at 1-, 3-, 6-, and 12- months post-operatively with clinical scores and at 12- months post-operatively with MRI.

Participant timeline is outlined in Table 1.

**TABLE 1 T1:** Participant timeline.

Procedure	Pre-op	1-month follow-up	3-month follow-up	6-month follow-up	12-month follow-up
Eligibility and informed consent	X	–	–	–	–
CMS	X	X	X	X	X
VAS	X	X	X	X	X
DASH	X	X	X	X	X
PASS	X	X	X	X	X
MRI	X	–	–	–	X
AE reporting	–	X	X	X	X

CMS, Constant-Murley Score for clinical and functional shoulder evaluation; VAS, Visual Analogue Scale for pain intensity; DASH, Disabilities of the Arm, Shoulder, and Hand for disability and symptoms of the upper limb; PASS, Patient Acceptable Symptom State evaluates whether patients perceive their state as satisfactory; MRI, Magnetic Resonance Imaging with Sugaya classification for re-tear assessment; AE, adverse events (traumas, falls…) recorded at each Follow up.

### Adverse events and assessment process

3.9

Adverse events are monitored throughout the study and at clinical follow-up evaluations. Standard safety and efficacy monitoring is performed through visits. Patients are requested to report any adverse events to the research staff. Every adverse event is recorded in the patient case report form (CRF). Serious adverse events are considered those resulting in death or being life-threatening, requiring hospitalization or intervention to prevent permanent impairment or damage; they are reported in accordance with the requirements of the Ethical Committee.

### Data collection methods

3.10

Patients’ clinical records (informed consent, hospital admittance, interventions, radiologic imaging and follow-up) are registered in SIR2020 (v. 3.1.0, Engineering Ingegneria Informativa S.p.A, Italy). The data manager, after having allocated patients following the randomization list, attributes a numerical code to patients, so that sensitive data will be made pseudo-anonymized and used in compliance with the in-force legislation regarding privacy. Study data of patient’s records are collected and managed using REDCap electronic data capture tools hosted at Yale University and in the MODA database with the assigned numerical code. Data are accessible only to the PI, co-PI and their authorized collaborators or to monitoring or auditing procedures or to the Ethics Committee and relevant health authorities. Results from *in vitro* activities obtained from each experiment are saved in an e-CRF form in the MODA folder with appropriate password and limited access to authorized personnel.

### Data management

3.11

Study data are stored in a password-protected MODA folder on a server that is hosted at the Rizzoli Orthopedic Institute. Data transfer is encrypted with all data de-identified. Only authorized trained research personnel specifically dedicated to data handling can access the database and ensure the correspondence of the electronic data with the original paper-based clinical scores and medical charts.

### Statistical analysis

3.12

To identify the minimum patient sample size, an *a priori* power analysis is performed (G*Power 3.1.9.6v software, University of Kiel, D) based on a previous study (2), which used the same ADM on *n* = 5 patients, obtaining a re-tear rate of 40%. Furthermore, Cai et al. (24) obtained a re-tear rate of 13.7% by combining the suture with orthobiological augmentation. The hypothesis of the present study was that the addition of orthobiologicals would result in a re-tear rate of 10%, thus yielding an OR value of 6.

By considering an odds ratio (OR) = 6.0 for re-tear rate between ADM-orthobiologics and ADM alone, 95% confidence and 0.80 power (Fisher’s exact test, onetail) *n* = 36 for both groups is computed. This patient size considers 20% of drop-out patients.

All demographics, clinical, MRI, biological, biomechanical, histological, follow up clinical data are recorded in the electronic dataset for further statistical analysis. The statistical analysis of the results is conducted using SPSS/PC + Statistics TM (SPSS Inc., United States) or the R software (R Core Team, 2021^3^) and the related packages necessary for conducting the analysis such as ggplot2 (25) for graphical data representation. A *p*-value < 0.05 is considered statistically significant.

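### The 0.80 power belongs to an unjustified one-tailed Fisher test, while the significance rule names no tail; reported two-sided, Fisher power after the planned loss is about 0.66 to 0.74

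*Protocol article*

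**What the plan says.** The main aim (section 2) is to "evaluate the therapeutic efficacy in terms of re-tear rate at 12 months", comparing ADM plus orthobiologics (Group B) with ADM alone (Group A). Section 3.7.1 makes this the primary endpoint: "The primary outcome is the re-tear rate on MRI at 1 year follow up".

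Section 3.12 takes 40% as the re-tear rate with ADM alone and assumes that "the addition of orthobiologicals would result in a re-tear rate of 10%, thus yielding an OR value of 6". The calculation is described by "95% confidence and 0.80 power" and by the test, Fisher's "exact test, onetail". The result is 36 patients per group, said to allow for 20% drop-out.

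The same section later gives one rule for all analyses: a p-"value < 0.05 is considered statistically significant". That rule names no tail. Section 3.12 neither explains the one-tailed choice nor says that the primary analysis will be one-tailed. Section 2 does state a directional hypothesis of fewer re-tears with the combination, but does not offer it as a reason for testing in one direction.

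**The concern.** The stated power is tied to one tail, and the analysis rule does not commit to that tail. A one-tailed and a two-sided p-value would both satisfy section 3.12, and they can lead to opposite primary conclusions at results close to the planned effect. If the usual two-sided p-value is reported, the trial does not have the power it claims once the planned drop-out has occurred. If the one-tailed test is kept, a higher re-tear rate in Group B could never be declared significant, whatever its size.

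**Working it through.** **Inputs** (section 3.12, with allocation from section 3.3): re-tear 40% in Group A and 10% in Group B; α = 0.05; target power 0.80; Fisher's exact test; 1:1 allocation; 36 per arm; 20% drop-out.

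**Effect size.** OR = (0.40/0.60)/(0.10/0.90) = 6.0, as stated.

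**Method.** Power is the sum, over all pairs (a, b) of re-tear counts, of Bin(a; n_A, 0.40) × Bin(b; n_B, 0.10) for tables with Fisher p ≤ 0.05. The p-value is hypergeometric, given the total number of re-tears. The two-sided p-value was computed both by point probability (summing all tables no more likely than the one observed) and by doubling the smaller tail.

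**1. The plan's own figure reproduces.** One-tailed Fisher at 0.05 gives 0.781 with 29 per arm and 0.801 with 30 per arm, so 30 evaluable are needed. Then 30 × 1.2 = 36. Dividing by the retained fraction gives 30/0.8 = 37.5, so 38.

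**2. Evaluable patients after 20% loss.** 36 × 0.8 = 28.8 per arm, or 72 × 0.8 = 57.6 in total. Plausible splits are therefore 28/28, 29/28, 28/29 and 29/29.

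**3. Fisher power at 40% versus 10%:**

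| Evaluable A/B | One-tailed 0.05 | Two-sided, point probability | Two-sided, doubling |
|---|---|---|---|
| 28/28 | 0.762 | 0.660 | 0.660 |
| 29/28 | 0.789 | 0.696 | 0.685 |
| 28/29 | 0.778 | 0.742 | 0.685 |
| 29/29 | 0.781 | 0.681 | 0.681 |
| 30/30 | 0.801 | 0.705 | 0.705 |
| 36/36 | 0.879 | 0.800 | 0.800 |

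After the planned loss, two-sided power is 0.66 to 0.74 and one-tailed power is 0.76 to 0.79. At 29/29 the shortfall from 0.80 splits into 0.80 − 0.781 = 0.019 from the drop-out inflation and 0.781 − 0.681 = 0.100 from the change of tail.

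**4. The conclusion can flip.** With 29 per arm, 10 versus 3 re-tears (34% versus 10%) gives p = 0.028 one-tailed and 0.056 two-sided; 8 versus 2 gives 0.039 and 0.079. Under the plan's own rates, the chance of a table significant only on one tail is about 0.10 at 28/28, 29/29 or 30/30. It is smaller for 28/29 by point probability (0.778 − 0.742 = 0.036).

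**5. Actual size of the one-tailed Fisher test.** The maximum rejection probability under equal rates is 0.029 (28/28), 0.032 (29/28 and 28/29), 0.027 (29/29), 0.028 (30/30) and 0.038 (36/36). All lie below the nominal 0.05.

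**6. An unconditional exact alternative.** Boschloo's test at 0.025 per side has power 0.756 (28/28), 0.737 (29/28), 0.749 (28/29), 0.776 (29/29), 0.743 (30/30) and 0.864 (36/36). After the planned loss this is about 0.74 to 0.78.

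**The case against.** **The tail is stated openly and fits a directional hypothesis.** Section 3.12 does not conceal the one-tailed choice, nowhere says that the primary test is two-sided, and is consistent with section 2. This stands: the power loss is conditional on a two-sided report. It does not settle the matter, because the significance rule leaves the tail open and an expected direction is not by itself a reason to rule out the other one.

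**The sidedness of the final test may sit in a statistical analysis plan that is not shown.** This is fair for the form of the final test. The tail, power and significance rule in section 3.12 were nevertheless fixed in the article. An analysis plan with a two-sided Fisher test would not have the published power after loss, and one that kept a single tail would need a justification the article does not give.

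**A reader might infer that the favourable-direction error is doubled from 2.5% to 5%.** That is only nominal. With the test the plan names, the actual size is about 0.03 at the expected sample sizes.

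**A reader might infer that 0.80 is true only for the one-tailed reading.** It is not. Two-sided Fisher reaches 0.80 with all 36 per arm evaluable, and one-tailed Fisher falls short of 0.80 at 28 to 29 per arm.

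**A reader might infer that harm would go unseen.** The article does not support this. Re-tear rates can still be reported and adverse events are recorded separately (sections 3.7.2 and 3.9). The limit is that the primary test could not call an excess in Group B significant.

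**Conclusion.** The point holds in a limited form and should be fixed. The one-tailed choice is unexplained and the significance rule does not say which tail applies. Reported two-sided, Fisher's test has about 0.66 to 0.74 power with 28 to 29 evaluable per arm, depending on the split and the two-sided definition, and 0.80 only with no loss. Quoting 0.66 to 0.68 alone would be too narrow, since that covers only equal arms.

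Not all of the shortfall comes from the tail. The ×1.2 inflation leaves the one-tailed test itself at 0.76 to 0.79.

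These figures assume the plan's 40% and 10% rates, 20% loss spread roughly evenly, and Fisher's test, the only test that section 3.12 names. The article does not show that the investigators intend a two-sided test, nor that the type I error is materially inflated.

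**What to change.** State in section 3.12 and in the analysis plan, before unblinding, that the primary comparison of re-tear at 12 months is two-sided at 0.05. Preferably use an unconditional exact test (Boschloo, 0.025 per side) and restate power at 20% loss as about 0.74 to 0.78. Other valid exact tests exist; this one recovers much of the power that Fisher's conservatism costs.

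If Fisher's test is kept, name the two-sided definition and restate power as about 0.66 to 0.74, with 0.80 only if nobody is lost. In either case report the risk difference with a two-sided 95% confidence interval.

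The cost is wording and a less favourable stated power; no extra patients are needed. This accepts power below 0.80 rather than restoring it: with two-sided Fisher, 0.80 after 20% loss would take 36/0.8 = 45 per arm, 90 in total.

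### If Fisher's exact test is also the primary analysis, Boschloo's exact test would add about 5 to 8 points of one-sided power at the expected 28 to 29 evaluable patients per arm

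*Protocol article*

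**What the plan says.** Section 3.7.1 of the protocol article defines the endpoint: "The primary outcome is the re-tear rate on MRI at 1 year follow up". Section 3.12 gives the sample-size inputs. A small earlier series with the same matrix is cited as "obtaining a re-tear rate of 40"%, and the orthobiologic addition is assumed to be one that "would result in a re-tear rate of 10%, thus yielding an OR value of 6". The calculation takes "95% confidence and 0.80 power" and Fisher's "exact test, onetail", and concludes that "36 for both groups is computed", with 20% dropout already included.

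On the analysis itself, section 3.12 names only the software (SPSS or R) and a significance threshold of p < 0.05, without a side. It names no test for the final comparison of re-tear rates.

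**The concern.** Fisher's test conditions on the total number of re-tears. This design fixes the two arm sizes, but not that total. With some 29 patients per arm the conditional distribution is coarse, so the test cannot come close to its nominal level and part of the permitted error goes unused.

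Boschloo's test ranks the tables by the Fisher p-value, then sets the cut-off so that the rejection probability, maximised over the unknown common re-tear rate, stays within the nominal level. The Fisher rule already satisfies that limit, so one-sided Boschloo rejects every table that Fisher rejects, and usually some more.

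At stake is power in a small single-centre trial. The planned effect is optimistic by the article's own evidence: the 40% rests on five patients, and the other cited study "obtained a re-tear rate of 13.7% by combining the suture with orthobiological augmentation", which is less favourable than the 10% assumed.

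**Working it through.** **Inputs (section 3.12 unless stated).** Re-tear rate 0.40 with ADM alone and 0.10 with orthobiologics; odds ratio (0.40/0.60)/(0.10/0.90) = 6.0, as stated. Alpha 0.05, power 0.80, one-sided Fisher. 36 per arm, 1:1 (section 3.3). Dropout 20%, so 36 × 0.8 = 28.8 evaluable per arm.

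**Method.** Enumerate all tables (a, b) of re-tears in arms of size n₁ and n₂.
- Power = Σ Bin(a; n₁, 0.40) × Bin(b; n₂, 0.10) over the rejected tables.
- True size = the maximum over a common rate p of Σ Bin(a; n₁, p) × Bin(b; n₂, p) over the same tables.
- Fisher rejects when the hypergeometric tail probability is ≤ alpha. Boschloo rejects when that probability is ≤ c, with c the largest cut-off that keeps true size ≤ alpha.

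**The plan's figure first.** One-sided Fisher gives 78.1% at 29 per arm and first reaches 0.80 at 30 per arm (80.1%). 30 × 1.2 = 36, the stated number.

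**One-sided 0.05, 40% vs 10%** (Group A : Group B evaluable)

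| Split | Fisher size | Fisher power | Boschloo size | Boschloo power | Gain (points) |
|---|---|---|---|---|---|
| 28:28 | 0.029 | 76.2% | 0.047 | 84.3% | 8.1 |
| 29:29 | 0.027 | 78.1% | 0.048 | 85.8% | 7.7 |
| 29:28 | 0.032 | 78.9% | 0.048 | 84.1% | 5.2 |
| 28:29 | 0.032 | 77.8% | 0.048 | 83.5% | 5.7 |
| 36:36 | 0.038 | 87.9% | 0.048 | 91.2% | 3.3 |

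Averaged over random 20% dropout from 36:36, power goes from about 78.7% to 84.6%, a gain of about 6 points.

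An example at 29:29: 9 re-tears against 3 gives a one-sided Fisher p of 0.0513 (not significant) and a Boschloo p of 0.0311.

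**Two-sided 0.05, 40% vs 10%** (the usual two-sided Fisher p, which sums all tables no more probable than the one observed; Boschloo built on that p)

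| Split | Fisher power | Boschloo power | Gain (points) |
|---|---|---|---|
| 28:28 | 65.9% | 75.6% | 9.7 |
| 29:29 | 68.1% | 77.6% | 9.5 |
| 29:28 | 69.6% | 73.7% | 4.1 |
| 28:29 | 74.2% | 77.8% | 3.6 |
| 36:36 | 80.04% | 86.36% | 6.3 |

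The average over random dropout is 72.2% against 76.0%, about 4 points. If the two-sided Fisher p is instead taken as twice the one-sided p, its average power is 68.1%, and the average gain is about 7 to 8 points. The two conventions agree when the arms are equal.

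**Sensitivity to the effect.** With 13.7% in place of 10%, at 29:29 and one-sided 0.05, power is 64.3% for Fisher and 74.2% for Boschloo.

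**The case against.** The strongest objection is that the article contains no error here. Fisher appears only among the sample-size inputs; the analysis text names software and a threshold. The primary test may well be set in a statistical analysis plan that is not shown. Fisher is a standard, valid test, and 36 per arm was computed with its conservatism built in. All of this stands. A reader might infer that the protocol commits the primary analysis to Fisher, but the text does not say so. The point is therefore conditional.

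A reader might also infer a gain of 8 to 10 points on the same 72 patients. The figures do not support that as a general statement. Gains of that order appear at equal arms of 28 or 29, mainly two-sided; one patient's difference between the arms brings them down to about 4 to 6 points. With all 72 evaluable they are 3.3 points one-sided and about 6 two-sided. Nor is Fisher's size always about half of alpha: at 36:36 one-sided it is 0.038/0.05 = 76%.

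Finally, changing test and side together hides the effect of each. Two-sided Boschloo at equal arms (75.6% and 77.6%) does no better than the one-sided Fisher that the article states (76.2% and 78.1%). The gain exists only when the two tests are compared at the same side.

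**Conclusion.** The point holds as a conditional efficiency improvement. If Fisher is the planned primary test, Boschloo's test at the same side gives more power at every expected split examined, with true error still at or below 5%. One-sided, the gain is 5 to 8 points at 28 to 29 evaluable per arm, and power moves from just below 0.80 to 0.835–0.858. Two-sided, the gain is about 4 to 10 points, and power stays below 0.80 at 0.74–0.78.

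This rests on the article's 40% vs 10%, on its 20% dropout leaving 28 to 29 per arm, and, for the averages, on dropout that is random and independent of outcome. The gain is free in patients but not in actual error: at 29:29 one-sided, the true maximum rises from 0.027 to 0.048, which the nominal level permits. It does not show that the stated sample size is wrong; that figure reproduces.

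**What to change.** Before unblinding, state the primary test in the protocol or analysis plan, and settle two choices separately.

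1. **Side.** State whether the p < 0.05 threshold is one-sided or two-sided.
2. **Test.** If Fisher was intended, name Boschloo's unconditional exact test at that side as primary, and keep Fisher as a sensitivity check. For a two-sided test, also state how the two-sided p-value is formed, since this changes the result when the arms are unequal.

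Then restate power at 28 to 29 evaluable per arm for the side chosen: about 0.83–0.86 one-sided or 0.74–0.78 two-sided, on 40% vs 10%.

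The cost is a line or two of text. No further patients are needed, and R, which section 3.12 already names, can run the test. The downsides are that it is less familiar to readers than Fisher, and that the actual type I error moves up towards, but not above, 5%.
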